# The effect of concentrated bone marrow aspirate in operative treatment of fifth metatarsal stress fractures; a double-blind randomized controlled trial

**DOI:** 10.1186/s12891-015-0649-4

**Published:** 2015-08-20

**Keywords:** Metatarsal, Stress fracture, Surgery, Bone marrow, Stem cells

## Abstract

**Background:**

Fifth metatarsal (MT-V) stress fractures often exhibit delayed union and are high-risk fractures for non-union. Surgical treatment, currently considered as the gold standard, does not give optimal results, with a mean time to fracture union of 12-18 weeks. In recent studies, the use of bone marrow cells has been introduced to accelerate healing of fractures with union problems. The aim of this randomized trial is to determine if operative treatment of MT-V stress fractures with use of concentrated blood and bone marrow aspirate (cB + cBMA) is more effective than surgery alone. We hypothesize that using cB + cBMA in the operative treatment of MT-V stress fractures will lead to an earlier fracture union.

**Methods/Design:**

A prospective, double-blind, randomized controlled trial (RCT) will be conducted in an academic medical center in the Netherlands. Ethics approval is received. 50 patients will be randomized to either operative treatment with cB + cBMA, harvested from the iliac crest, or operative treatment without cB + cBMA but with a sham-treatment of the iliac crest. The fracture fixation is the same in both groups, as is the post-operative care.. Follow up will be one year. The primary outcome measure is time to union in weeks on X-ray. Secondary outcome measures are time to resumption of work and sports, functional outcomes (SF-36, FAOS, FAAM), complication rate, composition of osteoprogenitors in cB + cBMA and cost-effectiveness. Furthermore, a bone biopsy is taken from every stress fracture and analysed histologically to determine the stage of the stress fracture. The difference in primary endpoint between the two groups is analysed using student’s *t*-test or equivalent.

**Discussion:**

This trial will likely provide level-I evidence on the effectiveness of cB + cBMA in the operative treatment of MT-V stress fractures.

**Trial registration:**

Netherlands Trial Register (reg.nr NTR4377)

## Background

Marines, soldiers and athletes are prone to fractures due to extensive and repeated stress on (usually weight bearing) bones [1–4]. These stress fractures develop over time and are therefore different than the more commonly accounted traumatic fractures. The damage caused by repeated forces on the bone outruns the natural remodeling process in loaded bones, resulting in a weak spot or ‘stress reaction’ and eventually a stress fracture [5–7]. Due to the increasing sports participation in the general population and awareness of their existence, these types of fractures are more frequently diagnosed. Of all stress fractures of the lower leg, the stress fracture of the fifth metatarsal has one of the highest incidences, namely up to 25 % [8]. This issue is amplified in the patients that depend on perfect physical condition like professional athletes. In a recent review of the literature, it is described that operative treatment of fifth metatarsal stress fractures results in smaller number of delayed unions or non-unions, compared to conservative treatment [9]. Still, the time to return to activity varies from 12 to 18 weeks [9–12].

Compared to a normal, traumatic fracture, stress fractures do not seem to heal via callus formation, but rather by primary bone healing with remodeling across the fracture line [7, 13, 14]. This process is slower with a higher propensity to fail, resulting in a complete fracture and refractory healing, similar to non-union [7, 14]. In traumatic fractures healing starts with formation of hematoma and therewith release of inflammatory cells. The next phase is recruitment of mesenchymal cells that differentiate into osteoblasts resulting in primary bone formation with callus production followed by secondary bone formation, with bone remodeling. In stress fractures, healing starts with the remodeling phase. Via early woven bone formation, callus is only formed along the exit point of the fracture towards the medullary cavity [15, 16].

Thus one of the major factors in bone repair seems to be an inflammatory response with the activation of Bone Marrow Stem Cells (BMSCs), which appears to be the initiating step in the cascade of bone repair. BMSCs give rise to the cells that form mesenchymal tissues like bone and cartilage [17, 18]. The exact role of BMSCs (available in cB + cBMA) in bone formation needs further clarification, but previous studies with BMSCs have provided evidence for new strategies of bone regulation [22, 24, 19], especially in delayed- and non-union fractures [20–26]. To our knowledge, there are no studies available for the role of cB + cBMA in stress fractures. In this study, the effect of adding cB + cBMA to operative treatment of MT-V stress fractures on the time to union will be assessed and compared to operative treatment alone. We hypothesize that surgery with adding cB + cBMA of MT-V stress fractures results in faster union times than surgery alone.

## Methods/Design

### Study design and informed consent

This study is a double-blind, randomized, placebo controlled, multicenter trial, which is conducted in accordance with the Declaration of Helsinki [27]. The methodology will follow the Consolidation of Standards of Reporting Trials (CONSORT) guidelines [28, 29]. Approval has been obtained from the local institutional review board Medical Ethical Commitee of the Academic Medical Center, Amsterdam (METC AMC, study reference number: NL44188.100.13 2013_182). Before study entry, all patients have to give written informed consent prior to participation.

### Randomization

Patients will be allocated to the intervention or sham-control group after signing an informed consent through a block randomization in random permutated blocks of 4, 6 or 8 patients using *“Castor edc”* [30]. Randomization will be performed online by the researcher, one day pre-operatively. At the end of the inclusion period there will be an equal number of patients in each randomization arm. Patients and X-ray assessors will be blinded to the allocation of treatment during the complete study. It is strictly forbidden for the blinded evaluator to discuss patient treatment with any study personnel. It is also strictly forbidden for study personnel to discuss treatment allocation with the patient. The key to the secured allocation data will not be broken until all patients have completed the study unless it is necessary for patient safety. This key is with an independent doctor. Patient data will be stored on hospitals’ server and only the researcher can see this data files which is stored independent of allocation data.

### Inclusion criteria

Patients will be considered to be included in this trial if they fulfill all of the following criteria:MT-V stress fracture diagnosed on X-ray (Fig. 1) or other radiologic imaging

**Fig. 1 Fig1:**
[figure not shown]
X-ray of MT-V stress fracture. **a**. AP view b. Oblique view. Stress fracture of the MT-V, located in the metaphyseal-diaphyseal junction also called zone 2; or just distally from the intrametatarsal joint (MT-IV/MT-V) in the proximal diaphysis also called zone 3 [45], with sclerosis seen on both fracture sidesSkeletally mature

### Exclusion criteria

Subjects will be excluded from this trial if they meet any of the following criteria:Expected non-compliance; patients who are unable to fill out questionnairesCavovarus deformity of the foot as measured on the Salzmann viewCurrent participation in another clinical trialSuffering from auto-immune diseaseReceiving biologicals, prednisolone or some kind of chemotherapy within the previous yearConcomitant painful or disabling disease of the lower limbNo informed consentFemales being pregnant or nursingKnown active malignancyPrevious surgery for the present MT-V stress fracture

### Device description

The bone marrow required for the cB + cBMA treatment will be harvested from patient’s own iliac crest through needle aspiration. Two 30 cc syringes will be filled with bone marrow. Utilizing the MarrowStim Concentration System® (Biomet Biologics: Fig. 2) the bone marrow aspirate will be processed in a centrifuge (together with a counterbalance, 3200 rpm for 15 min); the poor cell plasma will be separated from the nucleated cell concentrate and the cBMA is realized (Fig. 3). No bone marrow will be collected from the patients within the control group; only a sham procedure will be performed by creating a similar skin incision on the same location on the iliac crest, to maintain patients’ blinding.

**Fig. 2 Fig2:**
[figure not shown]
Inserting bone marrow aspirate into the device. Insert the bone marrow aspirate into the Marrow Stim device, before putting it in the centrifuge

**Fig. 3 Fig3:**
[figure not shown]
Bone Marrow Aspirate after centrifuging. Bone marrow aspirate after centrifuging (cBMA) with: *upper layer* = cell poor plasma; *middle layer* = nucleated cell concentrate; *lowest layer* = red blood cells

### Standard treatment and investigational treatment

Experienced foot and/or ankle or trauma orthopaedic surgeons will perform the surgeries of both groups, within 2 weeks after inclusion. In brief, the proximal fifth metatarsal stress fracture will be approached and a decortication along the fracture lines will be performed. Part of this material will serve as a bone biopsy and is send for histological examination. The stress fracture will be internally fixated, with use of a cannulated intramedullary compression screw. The remaining material from the decortication will be used as an internal bone graft. The patients in the intervention group only will receive the cBMA mixed with 2 ml untreated autologous peripheral blood (cB + cBMA), together with the internal bone graft and serving as a natural scaffold; it will be put into and around the fracture. Of the 6 ml cB + cBMA obtained, 4 ml will be added to the fracture site the other 2 ml is used for analysis.

Both groups will receive a similar rehabilitation protocol for the first 8 weeks after operation; first two weeks in a non weight bearing-cast, then 2 weeks in a weight bearing cast or walker allowed to have partial weight bearing, thereafter 4 weeks in a weight bearing cast or walker without restrictions.

### Outcome measures

The primary endpoint is the time to radiographic union in weeks.

The secondary endpoints are: time to clinical union, time to return to work and/or sport (in weeks), union rate at each time point (in %), patient function and satisfaction (SF-36, FAOS, FAAM), complication rate and cost-effectiveness (SF-HLQ), compared between intervention and control group.

During the operation a bone biopsy is taken. This will be histologically analyzed. From the obtained cBMA a 2 ml sample will be analyzed (flow cytometry and a multiplex assay for detecting CD 31, CD 34, CD 45, CD 90, CD 105, CD 166 amounts, CFU-F assay and mRNA analysis).

### Objectives and hypothesis

The main objective is to determine the effect of cB + cBMA on healing of surgically treated fifth metatarsal stress fractures. We hypothesize that intramedullairy screw fixation with cB + cBMA will generate a shorter time to union. Furthermore we hypothesize that the total costs are lower and that there will be a quicker return to sports or activities.

## Definitions

### Primary outcome

The primary outcome will be assessed on X-ray in different directions; on AP view, lateral view and an oblique view. The following will be scored by two single blinded evaluators (skeletal radiologist and orthopaedic surgeon): correct position osteosynthesis (yes/ no), fracture line visible (yes/ no), % of fracture line visible, union (yes/ no).

The X-rays will be acquired every 2 weeks until the 14^th^ week and, after that, only in the patients in which radiological union has not yet occurred as deemed necessary by the treating physician.

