### Data acquisition and follow-up

Participating patients will be assessed at the following time points (Table 1):

**Table 1 Tab1:** Schedule for screening and follow-up of included participants

Screening and Follow-Up Clinical and Radiographic Exams						
Action	Pre-operative	Intra-operative	Follow-Up Visit (biweekly 2-14 weeks)	Follow-Up Visit Until Union (biweekly) (>14 weeks, determined by physician)	6 month follow-up visit	1 year Follow-Up visit
Information letter	X					
Obtain written informed consent	X					
Complete eligibility checklist	X					
Complete medical history and baseline characteristics (form)	X					
Complete physical examination (form)	X		X	X	X	X
Surgery		X				
- Operative form (surgical information)		X				
- cB + cBMA preparation and administration		X				
- Bone biopsy fracture site		X				
Lab assessments	X					
Questionnaires	X		X		X	X
Radiographic assessment	X	X	X	X	X	X
Complication (form)	X	X	X	X	X	X
Adverse events, withdrawals & re-operation (form)	X	X	X	X	X	X

before inclusion: information letter, complete reliability checklistpreoperatively (after an enrollment period of two weeks): informed consent, complete reliability checklist, baseline characteristics (age, gender, weight, height, affected side, duration of symptoms, smoking status, AAS before symptoms and at preoperative assessment, past medical history, medication used), type of sport and profession, local physical examination with VAS, laboratory assessment (Hemoglobin levels, leucocytes, sodium, potassium, urea and creatinine), FAOS, FAAM, SF-36, EQ-5D, SF HLQ, X-ray (AP oblique and lateral);intraoperative: cB + cBMA preparation and administration, bone biopsy of the fracture site, right after internal fixation an X ray (AP, oblique and lateral) and an operative form (surgical information) with complications and (S)AEs if applicable;biweekly 2-14 weeks postoperatively: wound inspection, local physical examination with VAS, FAOS, FAAM, SF-36, EQ-5D, TiC, X-ray (best view for analyzing the fracture), resumption of sports and work, complications and (S)AEs;six months postoperatively: local physical examination with VAS, FAOS, FAAM, SF-36, EQ-5D, TiC, X-ray (best view for analyzing the fracture), resumption of sports and work, complications and (S)AEs;one year postoperatively: local physical examination with VAS, FAOS, FAAM, SF-36. EQ-5D, TiC, X-ray (best view for analyzing the fracture), resumption of sports and work, complications and (S)AEs

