If union is not yet achieved after 14 weeks, patients are seen as determined by the responsible physician. At every subsequent visit at least an X-ray is made to be able to evaluate the status of the fracture (primary outcome).

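### After week 14 the protocol gives no single X-ray schedule for the primary endpoint, so a late union date can depend on discretionary film timing that blinded reading does not protect

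*Protocol article*

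**What the plan says.** Outcome measures: "The primary endpoint is the time to radiographic union in weeks". The Primary outcome section has two blinded evaluators score union on films taken every 2 weeks up to week 14. For the period after that, the protocol article speaks in three places:

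- Primary outcome: films are taken "only in the patients in which radiological union has not yet occurred as deemed necessary by the treating physician".
- Table 1, column header: "Follow-Up Visit Until Union (biweekly) (>14 weeks, determined by physician". The table also marks a radiographic assessment at 6 months and at 1 year for every patient, and the visit list repeats this ("six months postoperatively: local physical examination with VAS, FAOS, FAAM, SF-36, EQ-5D, TiC, X-ray (best view for analyzing the fracture").
- Text below Table 1: "If union is not yet achieved after 14 weeks, patients are seen as determined by the responsible physician". It adds: "At every subsequent visit at least an X-ray is made to be able to evaluate the status of the fracture".

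On blinding, the Randomization section says: "Patients and X-ray assessors will be blinded to the allocation of treatment during the complete study". It names no other blinded party.

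**The concern.** A union can be dated only to a film, so the film schedule is part of how the primary endpoint is measured. Up to week 14 it is fixed and common to both arms. After week 14 the three texts do not agree. One gives no interval, one ties films to visits whose timing is left open, and one names an interval and a discretion in the same header. The word restricting late films to patients without union also does not fit with 6-month and 1-year films for all.

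Two gaps turn this from untidy drafting into a possible source of bias. First, the physician who decides on late films is not listed as blinded. Second, the Primary outcome section does not say whether further films depend on the blinded reading of union or on the physician's own view. Blinded readers protect how a film is read, but not the date on which it was taken. If late films were spaced differently in the two arms, for whatever reason, the arm filmed less often would appear to heal later. No analysis plan can recover films that were not taken.

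**Working it through.** **Inputs from the Sample size section.** Means 12 weeks (control) and 10 weeks (intervention), SD 1.88, power 90%, 20 per arm before and 25 per arm after 20% dropout, final significance level 0.049. A two-sided test is assumed.

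**The plan's own figure first.** Effect size 2/1.88 = 1.06. A two-sample t-test needs 19.6, so 20 per arm; power with 20 is 0.906 at 0.05 and 0.905 at 0.049. 20/0.8 = 25. The sample size reproduces and is not at issue.

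**Who is affected.** Share uniting after week 14 = 1 − Φ((14 − mean)/1.88), taking union times as normal.

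- Control: 1 − Φ(2/1.88) = 14.4%; 25 × 0.144 = 3.6 patients.
- Intervention: 1 − Φ(4/1.88) = 1.7%; 25 × 0.017 = 0.4 patients.
- Together 4.0 of 50.

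**Stress case, no true effect, mean 12 in both arms.** Union is dated to the first film at or after true union. Films are every 2 weeks to week 14, then every L weeks, with a film at week 26. The protocol gives no firm L, so these values are assumptions. At mean 12, 12.7% unite between weeks 14 and 16 and 1.6% between weeks 16 and 18.

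- 4 versus 2 weeks: a union in weeks 14–16 is dated to week 18 instead of 16. Bias ≈ 0.127 × 2 = 0.25 weeks, and about 0.26 with the small later tail.
- 6 versus 2 weeks: unions in weeks 14–16 are dated to week 20 instead of 16, and those in weeks 16–18 to week 20 instead of 18. Bias ≈ 0.127 × 4 + 0.016 × 2 = 0.54 weeks.

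Simulated type I error of the t-test at 0.049:

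| Late interval, one arm vs the other | Bias (weeks) | Type I error |
|---|---|---|
| 2 vs 2 | 0 | 5% |
| 4 vs 2 | 0.26 | about 6% |
| 6 vs 2 | 0.54 | about 7.5–8% with 20 per arm, 8.5–9% with 25 |
| 6 vs 6 | 0 | 5% |

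**Equal but sparse intervals, true difference 2 weeks, 20 per arm.** The mean recorded difference is 1.99, 2.21, 2.46 and 3.21 weeks for late films every 2, 4, 6 and 12 weeks, and power is 0.87, 0.86, 0.84 and 0.77. Sparse late films therefore stretch the estimate and lower the power even when both arms are treated alike.

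**The case against.** The strongest reply is that few patients are involved and the safeguards are partly there. On the design figures only about 4 of 50 reach week 14 without union, and the Secondary outcomes section expects most unions between weeks 6 and 14. Every later visit includes a film, and the 6-month film caps the delay for unions before then. An arm-wide split in film intervals is a constructed case, and nothing in the protocol points to one. All of this stands, and it limits the size of the problem.

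A reader might go further in three ways that the document does not support.

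- That the treating physician is unblinded, or is the surgeon who did the aspiration or the sham. The protocol says neither. It only omits this role from those named as blinded.
- That the physician's impression of union overrides the blinded reading and stops further films. The protocol does not say this. The restriction to patients without radiological union follows the description of the blinded scoring, so the blinded reading may well be what is meant. The text leaves it open.
- That type I error could reach 40% to 80%. Those figures need a 6- versus 2-week split and a mean of 13.5 to 15 weeks. The design mean is 12. The abstract does speak of surgical treatment "with a mean time to fracture union of 12-18 weeks", but the Background section gives the same 12 to 18 weeks as time to return to activity, so that range is weak support for a slower mean time to union.

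**Conclusion.** The concern holds as a gap in how the primary endpoint is ascertained. The three texts do not give one film schedule after week 14, and nothing in them keeps late film timing independent of allocation.

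On the plan's own assumptions the reach is small: about 4 of 50 patients, mostly controls if the treatment works. The assumed splits at mean 12 give 0.26 to 0.54 weeks of bias against a 2-week target, and type I error of about 6% to 9% in place of 5%. With equal intervals there is no bias under the null. The effect grows if union is slower than planned. These sizes rest on normal union times, SD 1.88 and the assumed intervals. They show what the wording permits and do not predict what will happen. This should be fixed, but it does not invalidate the design, and the sample size stands.

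**What to change.** Reconcile the Primary outcome section, Table 1 and the text below it into one endpoint-film schedule after week 14 that is the same in both arms and does not depend on allocation. The biweekly interval already in Table 1 is one candidate. Apply it to every patient not yet united on the blinded reading, until union or the 6-month film, and state that the blinded reading decides who continues. Say whether the 6-month and 1-year films are for everyone. Physicians remain free to order other films for care.

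The cost is a short amendment, a few extra films, and blinded readings returned in time to decide on the next film, for about 4 patients on the plan's assumptions and more if union is slower. The article says the trial is about to start including patients, so the change can still be made before late film dates accrue.

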### Secondary outcomes

Clinical union will be measured during physical examination. Pain on axial compression force and pain on the fracture site during palpation will be monitored through a patient-based VAS score. When patients still report significant pain, measured as a VAS > 3 on a Visual Analogue Scale from 0 to 10 [31, 32], clinical union is not yet achieved. Return to sports is defined as the time (in weeks) to resumption of weight-bearing sports after surgery and the level should be maintained for at least 30 days [33]; return to work is defined in the same way. When returned to sport, but activity level decreases to below the start level within 30 days after resumption, then this will be deemed as a failed return to activity and the date will not be counted. From the 6^th^ till the 14^th^ week, most unions are expected to occur. On each of these biweekly time points a union rate will be counted; number of unions at t = XXX divided by total sample size (%).

The SF-36 is a patient-administered, generic health related quality of life instrument [34, 35]. The FAOS was developed to assess the patients’ opinion about a variety of foot and ankle-related problems [36]. The results can be presented as an outcome profile. The FAAM is a 29-item questionnaire. The FAAM consists of 2 subscales: Activities of Daily Living and Sports [37].

Cost-effectiveness is analyzed using the The EuroQol (EQ-5D) [38, 39] and the SF-36, FAOS, FAAM as measurement for effectiveness of treatment. Costs are calculated from the SF HLQ [40, 41] and the cost of the investigated intervention. The questionnaire consists of 11 questions and provides information about labor (missing) costs and additional paid working hours.

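### Clinical union rests on an unconfirmed pain score of 3 or less, so a transient or already low score can date it too early

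*Protocol article*

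**What the plan says.** **The rule.** Under Definitions, Secondary outcomes, two provoked pains are scored: "Pain on axial compression force and pain on the fracture site during palpation will be monitored through a patient-based VAS score". The criterion is worded negatively: "When patients still report significant pain, measured as a VAS > 3 on a Visual Analogue Scale from 0 to 10", then "clinical union is not yet achieved". No other criterion for clinical union is given.

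**The neighbouring endpoints.** The same paragraph requires return to sport to hold for at least 30 days and discards the date if activity falls back within that time. Return to work is defined the same way. Clinical union has no such condition.

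**Entry.** The diagnosis rests on imaging ("MT-V stress fracture diagnosed on X-ray (Fig. 1) or other radiologic imaging"), with skeletal maturity also required. Neither the inclusion nor the exclusion list sets a pain level.

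**Timing of the scores.** Data acquisition and follow-up schedules the score before surgery ("local physical examination with VAS, laboratory assessment") and then at each early visit ("biweekly 2-14 weeks postoperatively: wound inspection, local physical examination with VAS"). Standard treatment and investigational treatment describes "first two weeks in a non weight bearing-cast, then 2 weeks in a weight bearing cast or walker", followed by four more weeks in a cast or walker, so protection runs to week 8.

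**Analysis.** Statistical methods counts weeks to radiological union from surgery, compares the arms with a t-test or equivalent, and applies the same parameter to clinical union.

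**The concern.** Clinical union is analysed as a date, so the result depends on how that date is set. Since no other criterion exists, the natural reading is that a score of 3 or less means union and that the first such visit supplies the date. Four of the seven biweekly scores (weeks 2, 4, 6 and 8) are taken during or at the end of the cast or walker period, and one good score there would be enough. A patient who enters with provoked pain of 2 or 3 needs no change in pain to qualify at the first postoperative visit.

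Time to clinical union would then partly measure visit-to-visit noise in a 0–10 self-report and the pain level at entry. Patients dated to week 2 or 4 widen the spread within both arms and shrink the difference between them.

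**Working it through.** **1. The plan's own figure.** No calculation is given for clinical union, so the primary endpoint's planning values serve as a reference. Sample size gives means of 12 and 10 weeks and an SD of 1.88. The effect size is 2/1.88 = 1.06. A two-sided t-test at 0.05 with 90% power needs 19.58, so 20 per arm (power 0.906), and 20/0.8 = 25 with dropout. The stated figures reproduce and this point does not affect them.

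**2. Early dating from transient low scores.** Assumptions, none from the article: true clinical union at week 12, low scores from then on, and an independent chance q of a score of 3 or less at each of the five earlier visits (weeks 2 to 10).

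- First-visit rule: chance of too early a date = 1 − (1 − q)^5.
- Confirmed rule: the first of two consecutive low scores falls before week 12, found by enumerating the visit patterns. A chance low score at week 10, followed by the true one at week 12, counts as early.

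| q | First visit: early | Mean recorded week | Confirmed: early | Mean recorded week |
|---|---|---|---|---|
| 0.05 | 22.6% | 10.6 | 5.7% | 11.8 |
| 0.10 | 41.0% | 9.4 | 12.5% | 11.6 |
| 0.20 | 67.2% | 7.4 | 28.3% | 10.7 |

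**3. The cast and walker period alone.** For an unhealed patient with chance p of a low score at each of the four visits to week 8, the first-visit rule gives 1 − (1 − p)^4. Two consecutive low scores among the four are rarer.

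| p | One low score by week 8 | Two consecutive |
|---|---|---|
| 0.05 | 18.5% | 0.7% |
| 0.10 | 34.4% | 2.8% |
| 0.20 | 59.0% | 10.4% |
| 0.30 | 76.0% | 21.6% |

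**4. Effect on the comparison.** Assume the planning values of step 1 also hold for clinical union with 20 per arm, and that a share f of each arm qualifies at week 2.

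- Difference in means = (1 − f) × 2.
- Variance in an arm with mean m = (1 − f) × 1.88² + f(1 − f)(m − 2)².
- For f = 0.10: difference 1.8. The variances are 3.18 + 9.00 = 12.18 and 3.18 + 5.76 = 8.94, so the average SD is √10.56 = 3.25.

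| f | Difference (weeks) | SD | t-test power |
|---|---|---|---|
| 0 | 2.0 | 1.88 | 0.91 |
| 0.10 | 1.8 | 3.25 | 0.40 |
| 0.20 | 1.6 | 3.99 | 0.23 |
| 0.30 | 1.4 | 4.44 | 0.16 |

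Simulating the mixture at f = 0.10 gives t-test power of 0.42. A Mann-Whitney test falls less, from 0.89 to about 0.7.

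**5. Type I error.** With no treatment effect and 10% or 20% of each arm scored at week 2, the simulated t-test rejects in about 0.046 and 0.053 of trials, close to the nominal 0.05.

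**6. One patient.** Dating one patient to week 2 instead of week 12 moves an arm mean by (12 − 2)/20 = 0.5 weeks, or (12 − 2)/25 = 0.4 weeks.

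**The case against.** **Sufficiency of a low score is not written.** The article says when union has not been reached. It does not say that a score of 3 or less is enough, that the first such score fixes the date, or that a later score above 3 is ignored. A reader might infer that a patient scoring 3 at week 4 and 6 at week 10 is recorded as united at week 4. Read literally, the rule says that this patient is not united at week 10. This stands: such early dating is permitted, not prescribed.

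**Met before surgery.** A reader might infer that the endpoint can be reached preoperatively. It cannot, because weeks are counted from surgery and the first postoperative score is at week 2.

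**Low-pain entrants are hypothetical.** The score is for provoked pain, the wording about patients who still have pain presupposes it at the start, and duration of symptoms is a baseline item. Recent surgery at the site also makes a low palpation score at week 2 less than automatic. This lowers the likely frequency but does not exclude such patients, and the article gives no figure.

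**Imbalance posing as a treatment effect.** This too is tempting and does not hold. Entry pain is balanced in expectation by randomisation, and chance imbalance is already within the test's error rate (step 5).

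**An article condenses.** Detail may sit in a fuller document. But this text is a definition, and its own paragraph protects two neighbouring dates with a 30-day rule. The lack of any counterpart for clinical union is therefore a weakness in what is stated.

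**Confirmation has a price.** After week 14, extra visits are for patients without radiological union, as the physician determines. A patient who first qualifies at week 14 may next be seen at six months. This stands, and the fix must cover it.

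**Conclusion.** The point holds as a weakness in the definition of a secondary endpoint. The criterion is stated only negatively, does not say whether one or both pain tests count, and has no persistence condition. It is applied from week 2 with no pain level set at entry, so a transient or already low score can date clinical union too early.

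The size depends on assumptions. For a 5% to 20% chance of a transient low score per visit, early dating falls from 23–67% of patients to 6–28% with confirmation. If 10% of each arm qualified at week 2, t-test power on this endpoint would fall from about 0.91 to about 0.40, and less with a rank test, which the phrase allowing an equivalent test leaves open. These figures need independent visits, true union at week 12 (steps 2 and 6) and planning values borrowed from the primary endpoint (step 4). None of that is stated for clinical union, and the real frequency of low scores is unknown.

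The consequence is lost precision and a less valid endpoint. The documents do not support a claim of inflated type I error. The primary endpoint and the sample size are not touched.

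**What to change.** **Definition.** State the rule positively: clinical union is the first postoperative visit with a VAS of 3 or less on both axial compression and palpation, sustained at the next scheduled visit and dated to the first of the two. For patients who first qualify at week 14 and have no earlier later visit, the six-month visit serves as confirmation.

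**Analysis.** Keep all randomised patients in the main comparison. Report by arm how many had a preoperative VAS of 3 or less. Excluding them should be a sensitivity analysis only: as the main analysis it would remove randomised patients from a trial of 50.

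**Cost.** A change of wording in the endpoint definition and analysis. The preoperative, biweekly and six-month scores are already scheduled. The article describes the trial as about to start recruiting, so on that description the rule could be set before any outcome data exist. The downside is that late first scores are confirmed only after a longer gap, about 12 weeks from week 14 to six months. Confirmation also reduces early dating without removing it, and does not by itself deal with patients whose pain was low throughout. The count by arm and the sensitivity analysis are there for them.
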